#### **14.1.2 Safety Endpoints**

A line listing of each subject with an adverse event will be generated. At the group level, the number and percentage of subjects having each AE will be summarized for each formula group. Secondary endpoints including stool characteristics, GI tolerance, and infant characteristics will be summarized using descriptive statistics and qualitatively compared to age appropriate reference values when appropriate.

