### **2.2.4. Primary Safety Objective**

The primary safety objective is to compare the frequency of adverse events (AEs) between the formula groups (BBN-102 w/o OPN vs Brand Formula).

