The plan is to use the 129 subjects randomized to Brand Formula in the first phase of the study. Assuming a 25% attrition rate, we estimate 96 subjects will meet the Per Protocol (PP) population criteria. This data will remain blinded through the enrollment of phase

two of the study. In phase two of the study, infants will be randomized to Brand Formula or BBN-102 w/o OPN in a 1:8 ratio. Assuming a 25% attrition rate and to obtain at least 90% power, approximately 10 subjects randomized to Brand Formula and 86 subjects randomized to BBN-102 w/o OPN Formula will be enrolled in phase two of the study. With the addition of the 129 subjects from phase one of the study, there will be approximately a total of 139 subjects enrolled in the Brand Formula group and 86 subjects in the BBN-102 w/o OPN Formula group. Infants will be stratified by sex to achieve balance of males and females within each formula group.

At the conclusion of the study, a post-hoc power analysis on weight gain will be conducted.

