## 6. Statistical Methods

The statistical analyses will be reported using summary tables, figures and listings (TFLs). Numbering for TFLs will be based on the recommended numbering convention provided by the International Conference on Harmonisation. Unless noted otherwise, all statistical tests will be two-sided with a significance level of  $\alpha = 0.05$ . Tests will be declared statistically significant if the calculated p-value is  $\leq 0.05$ . Continuous variables will be summarized with means, standard deviations, medians, minimums and maximums. Categorical variables will be summarized by counts and percent of subjects in corresponding categories. Missing values are not considered for percent calculations, unless stated otherwise. In those cases, footnotes will specify the percent basis. All summary tables will be presented by formula received. Select baseline tables may also include a total summary.

Individual subject data obtained via the electronic data capture (EDC) system and from external vendors will be presented in by subject listings.

The analyses described in this plan are considered *a priori*, in that they have been defined prior to the blind being broken and the database locked. Any analysis performed after breaking the blind will be considered post-hoc and exploratory. Post-hoc analyses will be labeled as such on the output and identified in the CSR.

All analyses and tabulations will be performed using SAS® version 9.4 or higher. Tables and listings will be presented in pdf and rtf format. Upon completion, all SAS programs will be validated by an independent programmer. The validation process will be used to confirm that statistically valid methods have been implemented and that all data manipulations and calculations are accurate. Checks will be made to ensure accuracy,

consistency with this plan, consistency with tables and consistency between tables and corresponding data listings.

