## 7. Analysis Populations

- Intent to Treat (ITT): All randomized subjects in the study based on the formula group they are randomized to.
- Per Protocol (PP): A subset of the ITT population. It will consist of all subjects who complete the feeding protocol without significant protocol violations, have weight measurements at both baseline and Week 16, and who consume a single non-study formula feeding no more than 10 times during the duration of 16-week study as documented on the Other Than Formula Feeding Log. Additionally, subjects who consume more than 3 complete days of non-study formula, defined as greater than 50% (4 feedings) of the number of feedings in a 24-hour period from non-study formula, will also be excluded from the PP population. Inclusion criteria states that four anthropometric Z-scores (weight for age, length for age, head circumference for age, and weight for length) had to be  $\geq 5^{\text{th}}$  and  $\leq 95^{\text{th}}$  percentile. If two or more of the four anthropometric Z-score inclusion criteria are not met, it will be considered a significant protocol violation and the infant will be excluded from the Per Protocol population.

Given that some sites rely on paper growth charts (hand plotting) of anthropometric measures, occasional small errors may occur with subjects just slightly outside the 5th or 95th percentile being enrolled in the study. If only one of the four anthropometric Z-score inclusion criteria are not met, it will be considered a minor protocol violation and the infant will remain in the Per Protocol population.

- Safety Population: The safety population will be comprised of any subjects who are randomized and consumed at least one feeding of study formula.

Classification into ITT or PP populations will be conducted prior to the database lock. All listings will be provided for the ITT population. A separate listing will be included on the set of subjects who are randomized but never intake the randomized formula before discontinuing from the study.

Since this study has a primary aim at demonstrating non-inferiority, the PP population will represent the primary analysis population to evaluate the treatment groups in terms of “efficacy”.

All clinical outcomes (primary and secondary) will be subject to analyses using both the PP and ITT population.

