### 11.1. Adverse Events

Adverse events (AE) summaries will only consider Treatment Emergent Adverse Events (TEAEs). TEAEs are defined as those adverse events with date of onset after formula intake and those existing adverse events that worsened during the study. If it cannot be determined whether the AE is treatment emergent due to a missing or incomplete (partial) onset date, the AE will be considered treatment emergent. Verbatim terms entered into the clinical database via the EDC system will be mapped to preferred terms and system organ classes using the Medical Dictionary for Regulatory Activities (MedDRA), version 23.0.

Each AE summary will be displayed by formula group. Summaries that are displayed by system organ class and preferred terms will be ordered by descending order of incidence of system organ class and preferred term within each system organ class. Summaries of the following types will be presented:

- Overall summary of the TEAEs which contain an overview of each item below.
- Subject count and incidence rate of TEAEs by MedDRA system organ class (SOC) and preferred term (PT).

- Subject count and incidence rate of TEAEs by MedDRA SOC, PT and highest severity. At each level of subject summarization, a subject is classified according to the highest severity if the subject reported one or more events.
- Subject count and incidence rate of TEAEs by MedDRA SOC, PT and closest relationship to study drug (Related/Not Related). Related AEs are those reported as “Related” or “Possibly Related”. At each level of subject summarization, a subject is classified according to the closest relationship if the subject reported one or more events. Adverse events with missing relationship will be considered related for this summary.
- Subject count and incidence rate of Serious TEAEs by MedDRA SOC and PT.
- Subject count and incidence rate of TEAEs leading to study discontinuation by MedDRA SOC and PT.

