#### 11.1.1. Adverse Events of Special Interest

An overall summary of number and percentage of infants with any physician-reported AE of special interest will be presented by formula group.

Subject count and incidence rate by highest severity and by causality will be presented for all physician-reported AEs of special interest, A by-patient listing of all AEs of special interest will be provided.

Standardized definitions for common AEs that may or may not be related to formula tolerance (stooling, spit-up, vomiting, GERD, crying, skin issues) were provided to all investigators. Comparisons between formula groups of the incidence of these AEs of special interest will be tested using Fisher’s Exact tests.

Time to first gastrointestinal event will be analyzed using Kaplan-Meier method by formula group. Kaplan-Meier estimates of the 25th, 50th, and 75th percentiles and the 95% confidence intervals of the median will be provided for each formula group.

| ADVERSE EVENT                    | DEFINITION                                                         |
|----------------------------------|--------------------------------------------------------------------|
| Stooling Issues           |                                                                    |
| Difficulty having bowel movement | Crying, fussing, or turning red when having a bowel Movement       |
| Hard stools                      | Healthcare professional diagnosis; pellet or hard rock-like Stools |
| Constipation                     | Less than 3 bowel movements in 7 days                              |
| Acute diarrhea                   | Runny or watery stools for less than 2 weeks                       |

|                                        |                                                                                                                                                                                                                                                                                                                                                                                                                                                                                                                                     |

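### SAP V4 plans no between-formula estimate or confidence interval for adverse events, the primary safety objective; the only comparison is a Fisher p-value for events of special interest

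*Supplement*

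**What the plan says.** SAP V4, section 2.2.4, sets the aim: "The primary safety objective is to compare the frequency of adverse events (AEs) between the formula groups", here BBN-102 w/o OPN against Brand Formula.

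The AE analyses that follow are these:

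- **Section 11.1** tabulates subject counts and incidence by formula group for treatment-emergent AEs (TEAEs): by system organ class and preferred term, by severity, by relatedness, for serious events, and for events leading to discontinuation. It specifies no test, difference or interval between formulas.
- **Section 11.1.1** covers stooling, spit-up/vomiting/GERD, crying and skin events: "Comparisons between formula groups of the incidence of these AEs of special interest will be tested using" Fisher's exact test. It also says: "Time to first gastrointestinal event will be analyzed using Kaplan-Meier method by formula group". The stated output of that analysis is each group's own percentiles and an interval for its own median, with no contrast between groups.
- **Protocol v5.2, section 14.1.2**, is descriptive only: "the number and percentage of subjects having each AE will be summarized for each formula group".

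On the level of testing, SAP V4 section 6 says: "Unless noted otherwise, all statistical tests will be two-sided with a significance level of" 0.05. On the analysis set, section 7 says: "The safety population will be comprised of any subjects who are randomized and consumed at least one feeding of study formula".

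**The concern.** The objective is to compare, but the plan never says by how much AE frequency differs or how precisely that difference is known. For all TEAEs, related TEAEs, serious TEAEs and discontinuations there is no between-formula statistic at all. For the tolerance events there is a p-value and nothing beside it.

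This is a growth and safety study with roughly 86 infants on the new formula. The useful safety question is how large an excess of, say, vomiting or constipation the data still allow. A p-value cannot answer that, and at these group sizes it can exceed 0.05 when the true excess is substantial. An interval answers it directly, and for most other comparisons this SAP already supplies one.

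**Working it through.** **1. What each comparison delivers in SAP V4**

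| Outcome | Section | Planned between-formula output |
|---|---|---|
| Mean daily weight gain (primary efficacy) | 9.1 | Difference with 95% CI, judged against 3 g/day |
| Growth velocities, z-scores, measurements | 9.2.1–9.2.3 | Difference with 95% CI and p-value |
| Formula intake | 9.2.4 | t-test with 95% CI and p-value |
| Inflammation markers (exploratory) | 9.3.1 | t-test with 95% CI and p-value |
| GI tolerance and ICQ scores (secondary safety) | 11.2, 11.2.6 | Difference or odds ratio with 95% CI and p-value |
| AEs of special interest | 11.1.1 | Fisher p-value only |
| Time to first GI event | 11.1.1 | Per-group percentiles only |
| All, related, serious and discontinuation TEAEs | 11.1 | None |

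Exploratory cytokines get an interval that the primary safety objective does not.

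**2. Group sizes**

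Section 5 expects that "there will be approximately a total of 139 subjects enrolled in the Brand Formula group and 86 subjects" will be in the BBN-102 group. These totals follow from its evaluable targets and 25% attrition: 104/0.75 = 138.7, rounded up to 139, and 64/0.75 = 85.3, rounded up to 86. The safety population needs only one feeding, so 139 and 86 are close to the best case for AEs.

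The documents state no power or precision for AEs. The only phase two power figure is about 90% for weight gain, and it reproduces closely. The standard error is 6.0 × √(1/104 + 1/64) = 0.953. Then 3/0.953 − 1.96 = 1.19, which corresponds to a power of 88.2%.

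**3. Chance that Fisher's test reaches p ≤ 0.05**

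For true rates p₁ (Brand) and p₂ (BBN-102), exact power is the sum over all tables (x, y) of Bin(x; 139, p₁) × Bin(y; 86, p₂), keeping the tables whose two-sided Fisher p is at most 0.05. The rates are assumptions, because the documents give none.

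| Assumed Brand → BBN-102 rate | Power | Doubling missed |
|---|---|---|
| 2% → 4% | 10.1% | 90% |
| 5% → 10% | 27.0% | 73% |
| 10% → 20% | 51.9% | 48% |
| 15% → 30% | 73.8% | 26% |
| 20% → 40% | 88.5% | 11% |

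With both groups at 10%, the test's true size is 3.7%, so it is somewhat conservative.

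**4. What an interval would add**

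- *Equal rates.* If both groups are at 10%, the approximate 95% half-width is 1.96 × √(0.1 × 0.9/139 + 0.1 × 0.9/86) = 8.1 points. With no observed difference, an excess of about 8 points could not be excluded.
- *A non-significant table (hypothetical).* Take 16/86 (18.6%) on BBN-102 against 14/139 (10.1%) on Brand. Fisher gives p = 0.073. The Wilson limits are 11.8% to 28.1% and 6.1% to 16.2%. Newcombe's interval for the 8.5-point difference runs from 8.5 − √(6.8² + 6.1²) = −0.6 to 8.5 + √(9.5² + 4.0²) = +18.8 points. The planned test would report only the p-value. The interval shows that an excess of up to nearly 19 points remains compatible with the data.

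**The case against.** The strongest points on the other side are these:

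- **AEs are customarily descriptive.** Protocol section 14.1.2 plans them that way, and counts by group let any reader compute a risk difference. This is partly right, since nothing is biased or lost. But the stated objective is to compare, the SAP already chose to test, and section 6 labels any analysis done after unblinding as post hoc and exploratory. An interval has to be written in beforehand to count as planned.
- **The miss rates rest on assumed event rates.** This stands. It would be tempting to say that a doubling is missed about half the time, but that holds only near 10% to 20%. Several special-interest definitions are broad, so common events are plausible, and at 20% to 40% the test detects the doubling 89% of the time.
- **The plan never equates a non-significant result with equal safety.** This also stands. A reader might infer that p > 0.05 will be reported as comparable safety. No section says so, and the SAP sets no decision rule for AEs. It simply offers nothing else from which to read the comparison.
- **An interval does not raise power.** This is true. Power follows from a sample size set for weight gain. The interval makes the remaining uncertainty visible without reducing it.
- **Section 11.2 already gives intervals for tolerance.** It does so for stool, fussiness, gas and ICQ scores, which overlap the stooling and crying events. Those serve the secondary safety objective and do not cover vomiting, GERD or skin events.

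**Conclusion.** The point holds as a gap in the reporting and interpretation of the primary safety objective. SAP V4 plans no between-formula estimate or interval for any AE, and this departs from the SAP's own practice for other outcomes. That finding needs no assumption about rates.

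The size of the problem does depend on rates. At 139 against 86 infants, the chance of missing a doubling runs from about 90% for a rare event (2% to 4%) to about 11% for a common one (20% to 40%), with 5% to 10% and 10% to 20% in between at 73% and 48%.

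Two further readings should be resisted. The absence of an AE margin or of AE-based sizing is not itself a fault: an estimate with its interval serves the objective without either. Nor does the gap touch the growth conclusion, which rests on a confidence limit against 3 g/day. The change is worth making because it costs almost nothing and answers the safety question better than a p-value alone.

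**What to change.** In SAP V4, sections 11.1 and 11.1.1:

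1. Add the risk difference (BBN-102 minus Brand) with a two-sided 95% confidence interval, naming one method, either Miettinen-Nurminen or Newcombe. Report it for any TEAE, related TEAEs, serious TEAEs, TEAEs leading to discontinuation, and each special-interest group (stooling; spit-up, vomiting and GERD; crying; skin).
2. State that AE frequency will be interpreted from the estimate and its interval, in particular the upper limit, and that a non-significant Fisher test is not by itself evidence of equal frequency.
3. Keep Fisher's p-values as supportive.

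The cost is a few sentences and some extra table columns, with no new data, visits, margin or sample size. The downside is that the intervals will be wide, so the safety statement will read less favourably than a bare non-significant p-value.

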## 11.2. Gastrointestinal Tolerance

Gastrointestinal tolerance (stool composition, number of stools per day, stool consistency, fussiness, gas, Infant Characteristics Questionnaire (ICQ) scores) will be compared between BBN-102 w/o OPN and Brand Formula. The studentized residuals for each endpoint will be assessed for normality using a histogram and quantile-quantile plot. If the normality assumption holds, then the gastrointestinal characteristic or general disposition score will be summarized by formula group and visit with descriptive statistics. Treatment effect will be compared using a mixed-effect model for repeated measures (MMRM) with sex, age, baseline value, formula, pooled site, visit, formula by pooled site interaction, and formula by visit interaction as factors. The covariance matrix will be chosen based on the AIC criteria to choose the covariance matrix that best fits the model. In addition, the formula effect by visit will be summarized. An alpha level of 0.05 will be used to test the formula effect. 95% confidence intervals and p-values will be reported on the difference of least square means for comparison of formula groups at each visit. The test for treatment effect of the score for the gastrointestinal characteristic or general disposition over the 16-week period will have the following hypotheses:

H0: There is no difference between the formula groups.

H1: There is a difference between the formula groups.

If departure from normality is detected, then the gastrointestinal characteristic or general disposition responses will be summarized by frequencies and percentages for each category by formula group and visit. Formula groups will be compared using a Multinomial Logistic Regression model with sex, age at enrollment, baseline value, formula, pooled site, visit, formula by pooled site interaction, and formula by visit interaction as factors. The default SAS covariance structure matrix (independent) for this model will be used. In addition, the formula effect by visit will be summarized. An alpha level of 0.05 will be used to test the formula effect. 95% confidence intervals and p-values will be reported on the odds ratio to compare formula groups at each visit. The test

for treatment effect of the score for the gastrointestinal characteristic or general disposition over the 16-week period will have the following hypotheses:

$H_0$ : Odds Ratio for formula groups = 1, no difference between the formula groups.

$H_1$ : Odds Ratio for formula groups  $\neq$  1, there is a difference between the formula groups.

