#### **11.2.4. Fussiness**

Two separate questions for fussiness will be assessed and reported at each visit. Fussiness in the past 24 hours will be coded as: 0=Not at all fussy, 1=Slightly fussy, 2=Moderately fussy, 3=Very fussy, and 4=Extremely fussy. Over the past 24 hours, fussiness compared to normal will be coded as: 0=Less fussy than normal, 1=About the same level of fussiness as always, and 2=More fussy than normal. Each score for fussiness over the 16-week study will be analyzed as described in section 11.2.

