Formula groups will be compared using a MMRM with sex, age at enrollment, baseline value, formula, pooled site, visit, formula by pooled site interaction, and formula by visit interaction as factors. The covariance matrix will be chosen based on the AIC criteria to choose the covariance matrix that best fits the model. In addition, the formula effect by visit will be summarized. An alpha level of 0.05 will be used to test the formula effect. 95% confidence intervals and p-values will be reported on the difference of least square means for comparison of formula groups at each visit.

The items which are included in the questionnaire but not included in scales above will be summarized individually with descriptive statistics by visit and formula group.

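### SAP V4 section 11.2 picks the model for each tolerance endpoint from residual plots without a criterion, its fallback does not suit several endpoints, and it differs from 11.2.6 on the ICQ

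*Supplement*

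**What the plan says.** SAP V4, section 11.2, sets its scope at the start: "Gastrointestinal tolerance (stool composition, number of stools per day, stool consistency, fussiness, gas, Infant Characteristics Questionnaire (ICQ) scores) will be compared". It then states the check that decides the model: "The studentized residuals for each endpoint will be assessed for normality using a histogram and quantile-quantile plot".

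- **If normality is accepted**, the model is an MMRM: "95% confidence intervals and p-values will be reported on the difference of least square means for comparison of formula groups at each visit".
- **If it is not**, the response is treated as categorical: "If departure from normality is detected, then the gastrointestinal characteristic or general disposition responses will be summarized by frequencies and percentages for each category". A multinomial logistic regression follows: "95% confidence intervals and p-values will be reported on the odds ratio to compare formula groups at each visit".

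Sections 11.2.1 to 11.2.5 (stool composition, number of stools, consistency, fussiness, gas) each refer back to 11.2 for the analysis. Section 11.2.6 does not. It sets out its own windows, hypotheses and model for the ICQ subscales: "Formula groups will be compared using a MMRM with sex, age at enrollment, baseline value, formula, pooled site, visit", with the interactions added and no normality check.

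Section 6 calls the planned analyses a priori because they are "defined prior to the blind being broken and the database locked". Protocol v5.2, section 14.1.2, plans only descriptive summaries for these endpoints, so it does not settle the model.

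**The concern.** The two branches are specified, but the trigger is not. No test, cut-off, reader, timing or default model is given. The residuals come from a model that contains formula, and the plan does not say that the plots are read without knowledge of group. Two analysts who both follow the SAP could report one item as a mean difference and as an odds ratio, with different p-values.

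The rule also works badly when followed to the letter. Several endpoints are short ordered scales, for which a normality check has only one honest answer. Others are continuous or nearly so, and the fallback asks for category frequencies that do not exist or are too many to use. For the ICQ, two sections of the same SAP give different instructions once non-normality is declared.

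At stake are the interpretability and reproducibility of the secondary safety objective on gastrointestinal tolerance.

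**Working it through.** The plan states no figure on this point, so there is none to reproduce. The check has a textual part and a numerical illustration.

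**1. Does the check suit each endpoint?** (Codings from SAP V4, 11.2.1–11.2.6; visit schedule from section 4.1.)

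| Endpoint | Possible values | Under the switch |
|---|---|---|
| Fussiness or gas compared with normal | 3 | Normal residuals impossible |
| Amount of gas | 4 | Same |
| Stool consistency; fussiness | 5 each | Same |
| Number of stools | 11 (0 to 10+) | A matter of judgement |
| Stool composition | Continuous; values below the detection limit set to that limit; visit 9 only | No categories for the fallback; no repeated measures for the MMRM |
| ICQ subscales | See step 2 | Fallback hardly workable; 11.2.6 says MMRM |

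A typical short item is coded "0=Less fussy than normal, 1=About the same level of fussiness as always, and 2=More fussy than normal". At any fitted value its residual can take only three values, so the residuals fall in bands whatever the formulas do.

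**2. ICQ sums.** Each item scores 1 to 7. A sum of k items runs from k to 7k, which is 7k − k + 1 values.
- 6 items (Fussy/Difficult): 42 − 6 + 1 = 37
- 4 items (Unadaptable): 28 − 4 + 1 = 25
- 3 items (Dull; Unpredictable): 21 − 3 + 1 = 19

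**3. Can the eye and a formal test part ways?** A Shapiro–Wilk test rejected normality in 100% of simulated samples for the 3- to 5-level items. A simulated six-item ICQ sum (168 infants, 500 runs, assumed item distribution) gave:

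| Assumed inter-item correlation | Shapiro–Wilk rejects | Median Q-Q correlation |
|---|---|---|
| 0 | 41.2% | 0.993 |
| 0.3 | 81.2% | 0.990 |
| 0.5 | 98.8% | 0.987 |

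A Q-Q correlation near 0.99 can look acceptable on a plot while the test rejects. Without a criterion, either branch could be defended.

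**4. One-visit illustration with no true difference.** Groups of 64 and 104 (SAP section 5), 10,000 runs, two-sided 0.05. A t-test on scores stands in for the mean comparison and a multinomial likelihood-ratio test for the fallback. The documents give no category distributions, so these are assumed. The error under free choice is the chance that at least one branch rejects: (t + multinomial + disagreement) / 2.

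| Assumed distribution | t | Multinomial | Disagree | Either rejects |
|---|---|---|---|---|
| 0.15, 0.70, 0.15 | 4.9% | 5.4% | 5.6% | 7.9% |
| 0.25, 0.45, 0.25, 0.05 | 5.2% | 6.0% | 6.9% | 9.0% |
| 0.35, 0.35, 0.20, 0.07, 0.03 | 4.9% | 6.5% | 7.9% | 9.7% |
| 0.05, 0.20, 0.50, 0.20, 0.05 | 5.1% | 6.5% | 7.9% | 9.8% |

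For the first row, (4.91 + 5.37 + 5.60) / 2 = 7.94. With a rank test in place of the multinomial test, the last column is 5.0–6.0%.

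**5. Repeated-visit illustration.** 139 and 86 infants (SAP section 5), eight post-baseline visits, 25% dropout and an assumed latent within-infant correlation of 0.2–0.4. There were 1,500 trials per setting, with no effect and with a 0.25 SD latent shift. The MMRM was approximated by a t-test on infant means, and a fallback that respects clustering by infant-mean ridits. The branches disagreed in 0.1–5.6% of trials, and free choice gave 5–6% error.

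**The case against.** The strongest reply is that both branches were written in advance, with covariates, alpha, effect measure and hypotheses. A residual check that selects between two named models is a familiar kind of pre-specified rule, so section 6 is not contradicted. That stands. A reader might infer that the tolerance analysis is not pre-specified at all, or that the model will be chosen by someone who knows the groups. The documents support neither inference: only the trigger is open, and on blinding they are silent.

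Second, for the 3- to 5-level items the branch is close to predictable, because normality must fail. That also stands. The real ambiguity lies with stool number, stool composition and the ICQ sums, and the disagreement rates above were not computed for those endpoints.

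Third, 11.2.6 is complete in itself and, as the specific section, can be read as governing the ICQ. That is the sensible reading, but 11.2 names the ICQ in its scope and nothing ranks one section over the other. The two diverge only if non-normality is declared.

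Fourth, these are secondary safety endpoints for which the protocol plans only description. This limits the weight of the point but does not remove it, since the SAP will report confidence intervals and p-values for them.

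**Conclusion.** The point holds as a SHOULD-level matter of specification. Section 11.2 leaves the model and effect measure of each tolerance endpoint to an unquantified reading of plots. Its fallback does not suit stool composition or the ICQ sums, and it differs from 11.2.6 on the ICQ if non-normality is declared. This part rests on the text alone.

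The numerical effect of the switch is modest: about 0–6% disagreement and 5–6% error if the fallback handles repeated records, and 5.6–7.9% disagreement with at most 8–10% error in the one-visit check. The last figure is an upper bound, because it assumes that the favourable model is always taken. All these figures rest on assumed distributions and on simple stand-ins; neither SAP model was fitted.

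A reader might infer a much larger cost. If the fallback treats each visit as an independent record, simulated disagreement is 11–24% and null rejection under the fallback is 15–28%. Those figures measure the neglect of within-infant correlation, which is a separate question, and should not be counted against the switch. They also assume naive standard errors: section 11.2 names an independent covariance structure but does not say how standard errors are obtained.

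The primary non-inferiority test on weight gain is untouched.

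**What to change.** Before unblinding, amend section 11.2 to delete the plot-based switch and name one model and one effect measure for each endpoint. A workable set is:

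- **ICQ subscales:** MMRM with mean differences. Keep 11.2.6 and remove the ICQ from the list in 11.2.
- **Number of stools:** MMRM with mean differences.
- **Stool consistency, both fussiness items, both gas items:** one categorical or ordinal model that allows for repeated records per infant, with its odds ratio defined. Either type will serve if it is fixed now; an ordinal model adds a proportional-odds assumption if a cumulative logit is used.
- **Stool composition:** a single comparison at visit 9, either log-transformed or rank-based, with the choice stated.

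Report the alternative model as a labelled sensitivity analysis. Residual plots can still be shown as diagnostics, without deciding which result is primary.

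The cost is SAP wording only; no data collection or visit changes. The downside is that the named model may not be the best-fitting one for every item, which the sensitivity analysis will show.
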